**Fig. 1 Fig1:**
[figure not shown]
Standard Protocol Items: Recommendation for Interventional Trials (SPIRIT) schedule of enrollment, interventions and assessments

The stepped-wedge, cluster-randomized trial is a form of cross-over design with unidirectional cross-over (from control to intervention phase) at different time points for each cluster (Fig. 2). Each cluster will contain one center. Randomization will determine the order in which each center will undergo the transition [15, 16]. In the first timeframe, all centers will deliver current practice (i.e. control). In the second timeframe, the center in the first cluster will start with algorithm-based best practice (i.e. intervention), while all other centers will still deliver current practice. In the third timeframe, the second cluster will implement the algorithm. Following this approach, we proceed until all centers have stepped over to the algorithm. In the last timeframe, all centers will deliver treatment according to the algorithm. Each cluster will contain one center; therefore, the number of sequences is equal to the number of participating centers and this will be 17. To ensure adequate implementation of the algorithm, a wash-in period was designed in which clinicians in the center will be intensively trained by the research team on the algorithm. To avoid contamination of centers still in the current-practice phase, local clinicians will only have access to the algorithm after cross-over to care according to the algorithm.

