The expected reduction in the composite primary endpoint was evaluated in two datasets. A relative reduction of 53% was observed in the study on management of pancreatic fistula (i.e. 34% after primary catheter drainage versus 73% after primary relaparotomy). Using the Dutch Pancreatic Cancer Audit data, centers were divided into four quartiles based on the incidence of the primary endpoint after pancreatoduodenectomy. The incidence was 21% in the worst-scoring quartile containing 292 patients from four centers. The incidence of the composite primary endpoint was 8% (i.e. relative reduction 62%) in the best-scoring quartile containing 331 patients who underwent pancreatoduodenectomy in five centers. Based on these outcomes, a relative reduction of 50% in the primary endpoint was used for the sample size in the PORSCH trial. This was the minimal reduction deemed clinically relevant by the members of the trial steering committee and stakeholders from the Dutch Pancreatic Cancer Group.

The required sample size was calculated using the formula for stepped-wedge designs using an expected incidence of 13.8%, a relative reduction of 50%, two-sided alpha of 0.05 and power of 0.80 [30]. The intra-cluster correlation (ICC) estimated from the Dutch Pancreatic Cancer Audit was 0.009 (95% CI 0.006–0.049). As the within-period and between-period ICC were the same, the cluster autocorrelation was set at 1 [31]. Table 3 provides the required sample size for different numbers of participating sites (i.e. clusters). This number dictates the inclusion time in this study design, which was based on the total number of pancreatoduodenectomies performed in the last 2 years according to the Dutch Pancreatic Cancer Audit. As each cluster will contain one of the 17 participating centers, the number of sequences is equal to the number of clusters. Based on the annual number of pancreatoduodenectomies performed in The Netherlands in 2014 and 2015, the planned study duration is 92 weeks to include the required sample size of 1186 pancreatoduodenectomies with complete enumeration (i.e. 5.1 weeks per step for 18 time periods). The total duration of the trial will be 96 weeks, including a 4-week wash-in period.

**Table 3 Tab3:** Required sample size for different numbers of participating centers

Number of centers	Cluster size^**a**^	Required sample size	Expected inclusions	Inclusion time^**b**^
14	5.9	1239	1239	28
15	5.1	1220	1224	25
16	4.5	1204	1224	24
17	3.9	1186	1193	22

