### Randomization, blinding and treatment allocation

Randomization is performed after obtaining consent for participation in this trial from the principal investigator and after approval from local (medical ethical) committees of every participating center was obtained. Centers are randomized by an independent statistician using R statistics software to determine the timing of cross-over from current practice to the algorithm [32]. Stratification at randomization is applied for center volume (>45 vs. ≤ 45 pancreatic resections a year, median value based on data from the Dutch Pancreatic Cancer Audit 2014–2015).

Local principal investigators are informed about the allocated time of cross-over of their center, but are blinded to the randomization sequence for all other centers. Blinding of treatment strategy for clinicians or study personnel is not feasible due to the study design. Primary outcomes will be assessed by individual members of an adjudication committee blinded to the intervention (i.e. whether this patient was treated before or after implementation of the algorithm). Patients will be coded by a numeric randomization key, and only the principal investigators have access to this key.

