The primary endpoint (i.e. composite of post-pancreatectomy bleeding, new-onset organ failure and death) is a binary variable that will be analyzed using mixed-effects logistic regression analysis. Secondary endpoints will be analyzed using crude and adjusted mixed-effects logistic regression analysis (for binary outcomes) or mixed-effects linear regression analysis (for continuous outcomes). Crude analysis will include a random intercept and random slope at the level of the hospital to adjust for the design, and no other covariates. Adjusted analysis will additionally include the following covariates: calendar time and time since cross-over as a continuous variable, predictors for postoperative pancreatic fistula (i.e. soft pancreatic texture, small-diameter pancreatic duct, increasing blood loss during pancreatic resection and underlying disease that is *not* pancreatitis or pancreatic adenocarcinoma [33]) and predictors for the primary endpoint (i.e. male gender, increasing age, American Society of Anesthesiologists (ASA) classification > 2, index pancreatic resection pancreatoduodenectomy; based on multivariable logistic regression analysis as presented in Table 4). Relevant model assumptions (such as distribution of residuals) will be checked for all models; if deviations from the analysis plan are required this will be described. Crude and adjusted odds ratios with 95% confidence interval and *p* value will be reported.

**Table 4 Tab4:** Factors associated with the composite primary endpoint in 1686 patients undergoing pancreatic resection in the Dutch Pancreatic Cancer Audit

Outcome	Univariable		Multivariable	
	OR (95% CI)	*P* value	OR (95% CI)	*P* value
Male gender	1.64 (1.20–2.23)	0.002	1.64 (1.19–2.27)	0.002
Age	1.02 (1.01–1.04)	0.003	1.02 (1.00–1.03)	0.04
BMI	1.00 (1.00–1.01)	0.52		
ECOG performance score		0.17		
2 vs. 1	1.29 (0.92–1.79)	0.14		
3 vs. 1	1.59 (0.95–2.66)	0.08		
4 vs. 1	0.44 (0.06–3.33)	0.43		
ASA classification (3 and 4 vs. 1 and 2)	1.87 (1.33–2.61)	< 0.001	1.79 (1.26–2.53)	0.001
Preoperative additional nutrition		0.05		
Oral vs. none	0.98 (0.70–1.38)	0.91		
Via nasogastric tube vs. none	1.74 (0.92–3.28)	0.90		
Via TPN vs. none	4.04 (1.17–14.02)	0.03		
Preoperative biliary drainage	0.97 (0.71–1.32)	0.82		
Distal pancreatectomy vs. pancreatoduodenectomy	0.50 (0.31–0.79)	0.003	0.58 (0.36–0.94)	0.03
Texture pancreas (hard/firm vs. soft/normal)	1.22 (0.86–1.73)	0.26		

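### The crude model is said to adjust for the stepped-wedge design but has no calendar-time term, so its odds ratio and p value absorb any secular trend

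*Protocol article*

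**What the plan says.** All references are to the protocol article, mainly the section Statistical analysis.

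- **Primary endpoint.** The composite "is a binary variable that will be analyzed using mixed-effects logistic regression analysis". The sentence does not say whether the crude or the adjusted form is meant.
- **Crude model.** The next sentences, which open with the secondary endpoints, define it by a "random intercept and random slope at the level of the hospital to adjust for the design, and no other covariates". The variable that carries the random slope is not named.
- **Adjusted model.** It adds calendar time, time since cross-over, predictors of pancreatic fistula and predictors of the primary endpoint. Time adjustment is therefore planned, but only here.
- **Reporting.** "Crude and adjusted odds ratios with 95% confidence interval" and p value are to be given, with no order of precedence.
- **Design.** Under Trial design, "the number of sequences is equal to the number of participating centers and this will be 17". All centers deliver current practice in the first timeframe and all follow the algorithm in the last.
- **Sizing.** Sample size calculation uses a stepped-wedge formula, "using an expected incidence of 13.8%, a relative reduction of 50%, two-sided alpha of 0.05 and power of 0.80". It adds that "The intra-cluster correlation (ICC) estimated from the Dutch Pancreatic Cancer Audit was 0.009" and that "the cluster autocorrelation was set at 1".

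**The concern.** In a one-way stepped wedge, exposure to the algorithm rises with calendar time by construction. A hospital random intercept, with or without a random slope on treatment, describes how hospitals differ from one another. It does not describe a drift shared by all of them, and that drift is what the design confounds with treatment. A fixed calendar-time effect is what adjusts for the design, so the reason the article gives for the crude model is wrong.

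If complications drift nationally over the 92 weeks of inclusion, the crude odds ratio credits that drift to the algorithm or charges it against it. The article attaches a p value to that estimate and does not rank it below the adjusted one, so a reader could take a partly before-after comparison as the randomized result.

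**Working it through.** **Inputs.** From Sample size calculation and Table 3: 13.8% versus 6.9% (difference 0.069), two-sided alpha 0.05, ICC ρ = 0.009, cluster autocorrelation 1, 17 hospitals, 18 periods, m = 3.9 patients per hospital-period, and 92/18 = 5.11 weeks per period. As a check, 17 × 18 × 3.9 = 1193, the expected inclusions in Table 3.

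**Method.** Generalized least squares on the hospital-period means, on the risk-difference scale. For each hospital V = [σ²(1−ρ)/m]·I + ρσ²·J, where I is the 18 × 18 identity matrix and J the matrix of ones. The variance of the effect is the treatment element of (Σ D′V⁻¹D)⁻¹, where D holds the intercept, treatment and, where included, time. Power = Φ(0.069/SE − 1.96). The article does not state its variance, so I took σ² = p̄(1−p̄) with p̄ = (0.138 + 0.069)/2 = 0.1035.

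**Step 1: reproduce the plan's figure (random intercept only).**

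| Model | SE | Power at m = 3.9 | N for 80% power |
|---|---|---|---|
| Calendar time, linear or categorical | 0.0245 | Φ(2.81 − 1.96) = 80.3% | 1183 (stated 1186) |
| No calendar time | 0.0187 | Φ(3.70 − 1.96) = 95.9% | 657 |

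The other rows of Table 3 also reproduce with time in the model: 1236 against 1239, 1216 against 1220, and 1199 against 1204. Under the other variances tried, the time-free N for 17 centers is 648 (average of the two arms) or 857 (control arm), never near 1186.

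**Step 2: how much trend the time-free model absorbs.** For a linear drift of a per period and no true effect, the time-free estimate has expectation a × c, where c is the treatment element of (Σ D′V⁻¹D)⁻¹ Σ D′V⁻¹t. This gives c = 7.16 periods, and 7.16 × 5.11 = 36.6 weeks, or 36.6/52 = 0.70 year. Simple averages bracket it. Pooled over hospitals, the mean period is 12.67 under the algorithm and 6.33 under control, a gap of 6.33. Within any one hospital, the mean period after cross-over exceeds the mean before it by 18/2 = 9. With a random treatment slope of SD 3 percentage points (assumed), c = 7.26, so the slope does not remove the trend.

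**Step 3: consequence under assumed trends.** The documents give no trend in the composite, so the range is an assumption. The shift is 0.138 × yearly fall × 0.70. The crude odds ratio is the odds at (0.138 − shift) divided by the odds at 0.138. The null SE, with σ² = 0.138 × 0.862, is 0.0211. With δ = shift/SE, type I error is Φ(−1.96 + δ) + Φ(−1.96 − δ).

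| Assumed relative fall per year | Shift | Crude OR, no true effect | δ | Type I error |
|---|---|---|---|---|
| 5% | 0.0049 | 0.96 | 0.23 | 5.6% |
| 10% | 0.0097 | 0.92 | 0.46 | 7.5% |
| 20% | 0.0194 | 0.84 | 0.92 | 15% |

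A separate 3000-run simulation (random intercept, 4 patients per cell) expressed the fall over the whole trial. Falls of 10%, 20%, 30% and 40% gave type I error of about 6%, 9%, 15% and 23% without time, and about 5% with linear or categorical time. That is the same order of magnitude.

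**Step 4: what the alternatives cost (power at m = 3.9).** Calendar time plus a random treatment slope gives about 78% at an assumed SD of 2 points and 76% at 3 points. Calendar time plus time since cross-over, without a random slope, gives about 75% in a linear approximation.

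**The case against.** The strongest reply is that calendar time is already planned. The adjusted model contains it, its odds ratio is reported beside the crude one, and the article nowhere calls the crude model primary. A condensed article may also leave the choice of primary model to an analysis plan that is not shown. This stands in part. A reader might infer that the trial ignores calendar time, or that the crude odds ratio is the headline result, and the documents support neither. What remains does not depend on the unseen plan: the crude definition, its stated rationale and the reporting of its p value are fixed here.

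Four further limits apply.

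- **Interval width.** A reader might infer that the crude interval is too narrow as a separate fault. With no secular trend, the time-free interval is valid and simply more efficient. The defect is bias when a trend exists.
- **Trend.** The Discussion describes management shifting away from relaparotomy, while the Background reports no such change in 2005–2013. Neither gives a trend in the composite. At 5% per year the inflation is negligible.
- **Random slope.** The standard errors in Step 1 use a random intercept only, whereas the article specifies a slope as well. At an assumed treatment-slope SD of 3 points, power is about 93% without time and 76% with it. A random slope on calendar time was not computed.
- **Volume stratum.** "Stratification at randomization is applied for center volume", and neither model lists volume, which may look like a second flaw. No bias from leaving it out has been shown, and both models carry a hospital random intercept.

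**Conclusion.** The point holds for the crude model as defined. Hospital random effects do not adjust for this design, and on the planned layout the time-free estimate carries about 37 weeks of any linear trend. The harm ranges from negligible (type I error 5.6% at an assumed 5% yearly fall) to material (15% at 20%), and a rising trend would bias the estimate the other way. The sizing supports the same conclusion: 1186 patients and 80% power correspond to a model with calendar time and not to the crude one.

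The figures assume equal cell sizes, a linear common trend, the stated ICC and a risk-difference approximation to the logistic model. They show that the reported crude estimate can be confounded, not that the trial's conclusion will rest on it.

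**What to change.** - Include calendar time, linear or categorical, as a fixed effect in the crude model for every endpoint, and withdraw the statement that hospital random effects alone adjust for the design. The two codings give the same SE here.
- Do not present a time-free odds ratio or p value as an effect estimate.
- State that a time-adjusted mixed-effects logistic model carries the primary conclusion.
- Keep time since cross-over for a secondary analysis. With it in the model, the treatment coefficient becomes the effect at the moment of cross-over, so naming the adjusted model as written would change what is estimated.
- Name the variable to which the random slope applies.

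**Cost.** This is a wording change, to be made before outcomes are compared by study phase. The interval is wider than the time-free one. Without a random treatment slope, it has the precision the sample size already assumed (80.3% power). With such a slope, power is somewhat lower, about 78% or 76% at the assumed SDs of 2 or 3 points, so the claim that no power is lost holds only in the first case.

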### Subgroup and sensitivity analyses

Analyses will be performed both on the group of patients undergoing pancreatoduodenectomy and on the entire group of all patients undergoing pancreatic resection. Additional subgroup analyses will be performed based on adherence to the study protocol (i.e. proportion of patients’ days in which the algorithm is followed), hospital volume (> 45 vs. ≤ 45 pancreatic resections a year), pathologic nature of disease (malignant disease), in patients with postoperative pancreatic fistula and in patients with a high risk of pancreatic fistula [34].

A sensitivity analysis will be performed to evaluate the impact on outcomes related to postoperative pancreatic fistula. To this aim, the adjudication will be asked if an outcome was related to postoperative pancreatic fistula and if this outcome could have been prevented by adherence to the algorithm. Two separate analyses will be performed on the Comprehensive Complication Index: one analysis including all complications and one adjusted analysis, in which interventions imposed by the algorithm (e.g. minimal invasive catheter drainage and use of antibiotic management for abdominal sepsis) will not be included in the calculation. A sensitivity analysis will be performed to evaluate the success of implementation. Centers will be divided into equally sized clusters based on the percentage of additional abdominal CT scans per patient after implementation, as compared with before implementation. Separate analysis will be performed for each group.

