### Outcomes

All outcomes are assessed up to 90 days after the index pancreatic resection or, if admission exceeds 90 days, up to hospital discharge. All relevant definitions are provided in Table 1. The primary endpoint is a composite of the following three major complications occurring after study intervention:
New-onset postoperative bleeding requiring invasive interventionNew-onset organ failure (i.e. pulmonary, circulatory or renal)Death

**Table 1 Tab1:** Relevant definitions

New onset	Not present any time in 24 h before study intervention; accounts for all outcomes
Mortality	Rate of death occurring within 90 days after index pancreatic resection or, if index admission exceeds 90 days, during admission
Organ failure [12]	
Pulmonary	PaO2 < 60 mmHg, despite FiO2 of 0.3, or need for mechanical ventilation
Circulatory	Systolic blood pressure < 90 mmHg, despite adequate fluid resuscitation, or need for inotropic support
Renal	Creatinine level > 177 μmol/liter after rehydration or need for hemofiltration or hemodialysis
Post-pancreatectomy hemorrhage (PPH)	Adapted from Wente et al [18]
Grade A	Occurring < 24 h after pancreatectomy (*early*) with no therapeutic consequences
Grade B	Both early (< 24 h) and late (> 24 h) requiring therapy (including fluid or blood transfusion and transfer to high-care unit), with non-life-threatening clinical condition. Includes early PPH requiring relaparotomy
Grade C	Occurring > 24 h after pancreatectomy (*late*) with severely impaired, life-threatening clinical condition requiring intervention
Comprehensive Complication Index (CCI)	This summarizes all postoperative complications, other than pre-existing complications, in a score from 0 (no complications) to 100 (death). The CCI can be readily computed on the basis of tabulated complications according to the Clavien-Dindo classification [19, 20]
Postoperative pancreatic fistula	Amylase in drain fluid on or after postoperative day 3 of at least three times the upper level of normal serum amylase [21]
Biochemical leak	Requiring no change in postoperative management, hospital stay not prolonged
Grade B	Persistent drainage > 3 weeks, change in postoperative management (i.e. catheter drainage, or angiographic procedure for bleeding, signs of infection without organ failure, no relaparotomy), all related to pancreatic fistula
Grade C	Grade B with reoperation, organ failure or death related to pancreatic fistula

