Leakage of pancreatic enzymes causes a local inflammatory response and thereby excretion of acute-phase enzymes like C-reactive protein, release of white blood cells and clinical signs of inflammation like fever, tachycardia and tachypnea [45, 46]. Amylase levels might be elevated when measured in abdominal drain fluid [10]. The abdominal drain might, however, not be in an adequate position to drain pancreatic leakage. In addition, abdominal drains are becoming more frequently omitted at the time of pancreatic resection or are removed in the early postoperative phase [47]. In these patients, signs of inflammation are the only early signs of postoperative pancreatic fistula. These signs are, however, nonspecific and often not recognized as potential pancreatic leakage, especially in centers where only a few patients with pancreatic fistula are seen annually [45]. We believe, however, that in these patients with a high risk of life-threatening complications, early abdominal CT should be performed and peripancreatic fluid collections should be managed aggressively with percutaneous drainage in patients showing signs of systemic inflammation [9, 48, 49]. This might result in an increased use of abdominal imaging and percutaneous catheter drainage procedures in the entire study population, with the intention of reducing severe bleeding, organ failure or mortality in a subset of patients. The outcomes of this trail will provide more insight into the “number needed to scan” or “number needed to drain” and the cost-effectiveness of intensified postoperative monitoring.

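### Comparing the two phases within fistula patients, adherence groups and CT-rise center groups conditions on variables measured after the algorithm starts, so those subgroup effects can be biased

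*Protocol article*

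**What the plan says.** All three groupings are in the protocol article, Subgroup and sensitivity analyses.

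- **Fistula.** Subgroup analyses are planned "in patients with postoperative pancreatic fistula and in patients with a high risk of pancreatic fistula".
- **Adherence.** "Additional subgroup analyses will be performed based on adherence to the study protocol", measured as the share of patient-days on which the algorithm was followed.
- **CT rise.** "Centers will be divided into equally sized clusters based on the percentage of additional abdominal CT scans per patient after implementation", relative to before, with a separate analysis in each group.

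Other sections show when these variables arise:

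- Table 1 (Outcomes) defines fistula by drain amylase on or after postoperative day 3. Grade B includes "change in postoperative management (i.e. catheter drainage, or angiographic procedure for bleeding" and also drainage persisting beyond 3 weeks. Grade C adds reoperation, organ failure or death related to the fistula.
- Under Intervention, daily evaluation by the algorithm begins on day 3. It uses drain amylase, prompts CT and drainage, and advises on drain removal.
- The Discussion expects that the algorithm might bring "increased use of abdominal imaging and percutaneous catheter drainage procedures in the entire study population".
- Fistula and the number of CT scans are also listed as secondary endpoints (Outcomes).
- Clinicians have no access to the algorithm before their center crosses over (Trial design).

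**The concern.** A subgroup comparison of two phases is interpretable when membership is settled before the intervention can act. Otherwise the patients compared may differ between phases for reasons that have nothing to do with benefit. The three groupings fail this test in different ways.

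- **Fistula patients.** The label is applied while the algorithm is running. Its grades overlap with an intervention that the algorithm prompts and with components of the primary endpoint. The mix of labelled patients may change at cross-over.
- **Adherence.** The quantity does not exist in the control phase. A group of adherent patients has no current-practice counterpart, and adherence may itself depend on the clinical course.
- **CT rise.** Each center's patients stay together, so membership does not shift by phase. The risk here is selection on noise. If patients with complications are scanned more, ranking centers on observed CT change partly ranks them on chance change in the outcome.

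What is at stake is how these results are read. Because the algorithm targets fistula, an odds ratio within fistula patients invites a causal reading, and the CT grouping invites one about good and poor implementation. Neither design supports it.

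**Working it through.** **The plan's own figure.** The article gives no numbers for these subgroup analyses. The sample size is not in dispute, but it supplies the design used in step 2. Inputs from Sample size calculation: "using an expected incidence of 13.8"%, "a relative reduction of 50%, two-sided alpha of 0.05 and power of 0.80", and "The intra-cluster correlation (ICC) estimated from the Dutch Pancreatic Cancer Audit was 0.009"; 17 centers, 18 periods. Individual randomization of 13.8% against 6.9% needs 305 per arm, 610 in total. The stepped-wedge design effect with k = 17 steps and n = 3.85 patients per center-period is

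[1 + 0.009(17n + n − 1)] / [1 + 0.009(8.5n + n − 1)] × 3(1 − 0.009) / [2(17 − 1/17)] = (1.615/1.320) × 0.0878 = 0.107.

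Then 610 × 0.107 × 18 ≈ 1178 (unrounded factors), against 1186 stated. The Hussey-Hughes variance gives 1182. The figure reproduces.

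**Step 1: relabelling in the fistula subgroup, no true effect.** Inputs:

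- Fistula before cross-over: 13% (Background, clinically relevant fistula).
- Endpoint risk in those patients: 44% (Table 2, severe fistula only).
- Extra share of all patients labelled after cross-over: 2%, 5%, 10% (assumed).
- Risk in the extra patients: 10% or 13.8% (assumed). The 10% is not extreme: with 13.8% overall and 13% of patients at 44%, the rest average (0.138 − 0.13 × 0.44)/0.87 = 9.3%.

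Subgroup risk after = (0.13 × 0.44 + x × r)/(0.13 + x). The odds ratio is against 0.44/0.56 = 0.786.

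| Extra x | r = 10%: risk, OR | r = 13.8%: risk, OR |
|---|---|---|
| 2% | 39.5%, 0.83 | 40.0%, 0.85 |
| 5% | 34.6%, 0.67 | 35.6%, 0.70 |
| 10% | 29.2%, 0.53 | 30.9%, 0.57 |

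The same formula run the other way shows that direction is open. Suppose 2% of patients at 10% or 13.8% risk lose the label, for example because fewer have drainage beyond 3 weeks. The risk becomes (0.0572 − 0.0020)/0.11 = 50.2% or (0.0572 − 0.00276)/0.11 = 49.5%, and the odds ratio 1.28 or 1.25.

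**Step 2: center groups by CT rise, no true effect.** Simulation with 17 centers, 18 periods, 3.9 patients per center-period (Table 3) and 13.8% risk in both phases. Assumed: 0.5 CT per patient without an event, 1.5 to 2.5 with one, mean rise 0.3 CT per patient, between-center SD of the rise 0 to 0.4, three groups. There were 4000 runs per scenario, using crude pooled odds ratios rather than the mixed model.

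| Group by observed rise | Mean OR across scenarios |
|---|---|
| Lowest third | 0.72-0.85 |
| Middle third | 1.01-1.04 |
| Highest third | 1.18-1.50 |

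**Step 3: adherence.** No arithmetic applies. The measure is the share of patient-days on which the algorithm was followed, and the algorithm is withheld before cross-over. The article does not say whether grouping is by patient or by center. By patient there is no control group; by center it is still a grouping on post-implementation behavior.

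**The case against.** The strongest reply is that these are secondary looks with sound companions. The primary analysis covers the whole population by intention to treat. A fistula-related version of the primary endpoint, judged by a blinded committee in all patients, is a secondary endpoint. One analysis of the Comprehensive Complication Index leaves out interventions imposed by the algorithm. A high-fistula-risk subgroup is planned, and interaction tests and labelling often belong in the SAP.

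Much of this stands, and it limits the point to three analyses. It does not remove it: the companions answer other questions and do not repair a phase comparison within fistula patients, and the article states the three groupings without caveat.

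Two stronger readings are tempting. A reader might infer that fistula patients after cross-over must be milder, so that the algorithm will look falsely effective. The documents do not show this. Fistula is defined first by drain amylase, not by drainage, and advice on drain removal could reduce grade B labels. A reader might also take 44% as the risk of every fistula patient. Table 2 restricts it to severe fistula, and it matches the drainage and relaparotomy groups: 0.73 × 34% + 0.27 × 73% = 44.5%. It serves only to illustrate.

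Nor do the documents state that centers with worse outcomes scan more, or that adherence follows severity. Both are plausible assumptions.

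**Conclusion.** The point holds for the three named comparisons. Each conditions on something determined after the algorithm starts, so a difference between phases within these groups cannot be read as an effect of the algorithm.

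The possible distortion is not negligible. With no true effect, the fistula-subgroup odds ratio lies between 0.53 and 0.85 for 2% to 10% extra labelling, and above 1 if low-risk patients lose the label. These values rest on the assumed labelling shift, the assumed risk in the shifted patients, and a 44% risk borrowed from severe fistula. The CT-rise values rest on patients with events being scanned more. True size and direction cannot be derived from the documents.

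The primary analysis, the sample size, and the subgroups by hospital volume, pathology and high fistula risk are not called into question.

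**What to change.** 1. Make the planned high-fistula-risk subgroup the inferential fistula subgroup, and state that it is defined only by pre- and intra-operative factors. The fistula predictors listed under Statistical analysis (texture, duct diameter, blood loss, underlying disease) are of this kind. Test it as an intervention-by-risk interaction in the full model with calendar time.
2. Report the comparison within patients with postoperative fistula as descriptive only, without a p value for the phase comparison, and show detected fistula rates by phase beside it.
3. Report the adherence and CT-rise comparisons as descriptions of implementation, also without phase-comparison p values. A different implementation measure would not cure the problem, because it too would be observed after cross-over.

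The cost is a change of wording in the analysis plan; the data are already planned for collection. The downside is that these three comparisons carry no p value.
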